### Safety assessment

3.3

In China, Shenling Baizhu Powder has a history of over 900 years, and the dose used in this trail is within the recommended range according to the People's Republic of China Pharmacopeia (2015 edition). In addition, we will assess the safety of Modified Shenling Baizhu Powder using a range of measures, including subjective descriptions and laboratory tests, with particular attention to gastrointestinal intolerance and cardiac, hepatic, and renal impairment, from enrollment through follow-up.

### Compliance

3.4

Upon randomization of participants, investigators at the study site will use all reasonable efforts to follow up with participants throughout the study. Adherence to the intervention will be monitored on each visit, and participants will be required to have all study containers returned with any unused granule packets, including all empty containers. Messages will be sent prior to each visit via WeChat or phone to remind participants of the impending data collection. Furthermore, ongoing support will be offered to participants during the follow-up phase, including free registration and treatment counselling.

### Adverse events

3.5

Any adverse events will be recorded in case report files (CRF) irrespective of their relationship to the study intervention. The intervention will be stopped immediately in the event of any serious adverse event. The timing of the intervention, severity, relationship to the drug, and actions taken in accordance with the China Food and Drug Administration (CFDA) Standard Operating Procedures (SOPs) will be documented in detail. Furthermore, severe adverse events shall be reported to the Steering Committee and Ethics Committee in 24 hours.

### Data management and quality control

3.6

All records will be collected in the CRFS and filled out by a trained and qualified investigator. The original record will not be altered once the CRF is completed, even if any modifications are made. The clinical inspector will review the completed CRFs. Data entry and management will be directed by a medical statistics specialist. To ensure data accuracy, 2 data managers will independently enter and proofread data. Once the database created is reviewed and confirmed to be correct, the data will be locked by the principal investigator and statistical analysts. The locked data or files will not be altered thereafter and will be presented to the research team for statistical analysis. Data monitoring will be the responsibility of The Sichuan TCM evidence-based Medicine Center (Chengdu, China), which has no competing interests. Data will be reviewed in the middle of the trial by The Department of Science Research of the Hospital of Chengdu University of TCM which is independent of the investigators.

### Statistical analysis

3.7

The intention to treat principle will be followed for all data analysis. The Statistical Package for the Social Sciences version 22.0 (SPSS 22.0, Chicago, IL) will be used to analyze the data. The analysis method should be based on the characteristics of the data distribution: The measurement data will be expressed as mean ± standard deviation and normal distribution, paired *t* test will be used for comparison before and after treatment, *t* test will be used for between-group comparisons (homogeneity test of variance will be performed with 0.05 as the test standard), and rank sum test will be used for comparison between groups. Chi-square test will be used for enumeration data, and rank-sum test will be used for grading data. Bilateral tests will be used for all tests, with *P* < .05 indicating a significant difference. For baseline data, the full analysis set (FAS, including completed cases and dropout cases, excluding censored cases) is used, and the full analysis set and the per-protocol set(PP set, including completed cases, excluding dropout cases and censored cases) are used for efficacy evaluation, which can enhance the reliability of trial results when the conclusions of the two analyses are consistent. When inconsistencies arise, differences should be fully discussed and explained. In the analysis of the full analysis set, the missing data are substituted by the method of sequence mean value.

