### Sample size

2.4

The sample size was calculated on the primary outcome (the forced expiratory volume in 1 second (FEV1) at 18 months). According to the previous literature,^[10]^**t**he mean value of FEV1 in the control group is estimated to be 2.54 with a standard deviation of 0.65. After the herbal treatment the mean value of FEV1 in the experimental group is 2.83 with a standard deviation of 0.73. The calculation of the sample size for the experimental and control groups of each was 121 cases using the software Power Analysis and Sample Size version 11.0 (PASS 11.0). Altogether, 268 participants are recruited at a 10% dropout rate. For the actual study, 135 cases per group will be included.

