### Treatment plan

3.1

Standards Western medicine will be used for both groups. According to GOLD^[4]^ and the Guidelines for the Diagnosis and Treatment of Chronic Obstructive Pulmonary Disease (Revised 2013),^[13]^ participants will receive inhalation treatment with tiotropium bromide powder (Si Li Hua, Boehringer Ingelheim Pharma GmbH & amp; Co. KG [Germany], 18 μg×30 capsules), 18 μg per inhalation, once a day. Also, the proper use of inhalants will be taught to all participants, who would also have to stop smoking and prevent colds. Throughout the study, patients are not allowed to receive other COPD-related medications or herbal treatments except in emergencies.

Experimental group: Participants will take 10 g Modified Shenling Baizhu Powder 3 times daily, dissolved in 100 mL of warm water, for 6 months.

Control group: participants will receive 10 g placebo granules 3 times daily, dissolved in 100 mL of warm water, for 6 months. The measurements will be in accordance with the experimental group.

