### Outcome measures

3.2

Primary outcome: FEV1 after bronchodilator use at 1, 3, 6, 9, 12, 15, 18 months

Secondary outcomes: at 1, 3, 6, 9, 12, 15, 18 months

1.the declines, the between-group difference in the change from baseline to 18 months in FEV1 before bronchodilator use, FVC, FEV1/FVC, FEV1%pred after bronchodilator use;2.the changes in mMRC score, CAT score, SGRQ score;3.Frequency, interval, duration, and severity of COPD exacerbations; time to first COPD exacerbation; and the use and cost-benefit analysis of rescue medications; smoking status; safety assessment.

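### The between-group test planned for post-bronchodilator FEV1 makes no use of the baseline value: it is valid but loses precision, its form is left to the data, and the added within-arm paired tests do not compare the arms

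*Protocol article*

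**What the plan says.** Section 3.7 (Statistical analysis) assigns these methods:

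- Between groups, a t "test will be used for between-group comparisons (homogeneity test of variance will be performed with 0.05 as the test standard"). A rank-sum test is also named for between-group comparison. The sentence is garbled and does not say when it applies, but the section opens by making the method depend on how the data are distributed.
- Within groups, a paired t "test will be used for comparison before and after treatment".
- No covariate, ANCOVA or repeated-measures model appears anywhere in the article.

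Section 3.2 (Outcome measures) makes the primary outcome the FEV1 value itself: "Primary outcome: FEV1 after bronchodilator use at 1, 3, 6, 9, 12, 15, 18 months". Changes from baseline appear only among the secondary outcomes.

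Section 2.4 (Sample size) says: "The sample size was calculated on the primary outcome (the forced expiratory volume in 1 second (FEV1) at 18 months"). Its inputs are raw means in each arm: "mean value of FEV1 in the control group is estimated to be 2.54 with a standard deviation of 0.65" and "mean value of FEV1 in the experimental group is 2.83 with a standard deviation of 0.73".

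Section 3.1 (Treatment plan) says: "Standards Western medicine will be used for both groups". This is inhaled tiotropium, and participants in both arms are also told to stop smoking.

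**The concern.** FEV1 in litres differs widely between people for reasons unrelated to treatment. Section 2.8 admits both sexes from 40 to 85 years, and the SDs used for sizing are 0.65 and 0.73. A participant's own starting value should explain part of that spread. It is available at no cost, because inclusion criterion 2 in section 2.8 requires post-bronchodilator spirometry. A comparison of raw 18-month values leaves this explainable spread in the error term. The confidence interval is then wider than it need be, and the trial is less able to detect an effect smaller than the one assumed.

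Two lesser matters sit in the same paragraph. Two tests are named for one comparison, and the observed data are to decide between them. The t test compares means and the rank-sum test compares distributions, so the quantity being tested is not fixed in advance. The paired tests describe change within an arm, which mixes any effect of the herbal product with tiotropium, stopping smoking and regression to the mean. A result significant in one arm and not in the other could be misread as a treatment effect.

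**Working it through.** **Inputs from the article.** Means 2.54 and 2.83 (difference 0.29), SDs 0.65 and 0.73, 121 per arm before dropout and 135 after (section 2.4); two-sided 0.05 (section 3.7).

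**Inputs that the article does not give.** Power; the correlation r between baseline and 18-month FEV1 (taken as 0.5 to 0.9); any effect other than 0.29 L (0.15 L is used as an illustration).

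**1. Reproducing the plan's figure.** Pooled SD = √((0.65² + 0.73²)/2) = 0.691. Standardised difference = 0.29/0.691 = 0.42. For an unadjusted two-sample t test (noncentral t), power is 0.8992 at 120 per arm and 0.9016 at 121. The stated 121 is therefore the unadjusted t test on raw FEV1 at 90% power. At 80% power the normal formula gives only 90 per arm. Baseline plays no part in the sizing.

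**2. Precision as planned.** SE of the difference = 0.691 × √(2/121) = 0.0889. Difference detectable with 80% power = (1.960 + 0.842) × 0.0889 = 0.249 L.

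**3. Precision with baseline adjustment.** The residual SD becomes 0.691 × √(1 − r²), and the share of variance removed is r². At 121 per arm:

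| r (assumed) | Variance removed | Residual SD | Detectable difference, 80% power | Power if the true effect is 0.15 L (assumed) |
|---|---|---|---|---|
| no adjustment | 0% | 0.691 | 0.249 L | 39% |
| 0.5 | 25% | 0.599 | 0.216 L | 49% |
| 0.7 | 49% | 0.494 | 0.178 L | 65% |
| 0.8 | 64% | 0.415 | 0.149 L | 80% |
| 0.9 | 81% | 0.301 | 0.109 L | 97% |

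Detectable differences use the normal formula, and powers use the noncentral t distribution.

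**4. Chance baseline imbalance.** Take 0.691 as the baseline SD too (an assumption, since it comes from the follow-up figures). With 135 per arm the baseline difference has SE 0.691 × √(2/135) = 0.084 L, a 95% range of ±0.165 L. The expected carry-over into the unadjusted 18-month difference is r times the imbalance. At r = 0.8 this is 0.8 × 0.165 = 0.132 L, or 0.132/0.29 = 45% of the planned effect.

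**5. Paired tests.** Suppose that both arms change equally and each paired test has power p. The chance that exactly one arm is significant is 2p(1 − p), which reaches 50% at p = 0.5 although the arms do not differ.

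**The case against.** The case for the plan is that its test and its sample size agree with each other. Under 1:1 randomisation the unadjusted t test is unbiased, its standard error already allows for chance imbalance, and it has about 90% power at the only effect that the article states. All of that stands. It limits the point to efficiency and prespecification.

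Several stronger readings are tempting, and the article does not support them:

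- *Most of the precision is wasted.* This needs r, which the article does not give. More than half of the variance is removed only if r exceeds √0.5 = 0.71, and the detectable difference is more than halved only if r exceeds √0.75 = 0.87. High values are plausible for FEV1 in litres in the same people, but that is an assumption.
- *The trial is underpowered for realistic effects.* No smaller effect is given; 0.15 L is illustrative.
- *Baseline imbalance passes in full into the result.* It carries over in proportion to r.
- *A normality pre-test decides the test.* Only the variance-homogeneity test is named. A distribution-based choice is inferred from the general wording. An analysis plan not shown might settle the trigger for the rank-sum test.
- *Baseline is ignored throughout.* Section 3.2 already treats pre-bronchodilator FEV1, FVC, FEV1/FVC, FEV1%pred, mMRC, CAT and SGRQ as changes.
- *Efficacy will be claimed from the paired tests.* The article does not say so, and between-group tests stand beside them. The harm is a risk of misreading.

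That an unseen analysis plan may add detail does not remove the point. Section 3.7 does name its methods, and they make no use of baseline.

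**Conclusion.** The point holds as a recommendation that should be taken up. The planned comparison of raw post-bronchodilator FEV1 is valid, with about 90% power (inferred) at 0.29 L, but it is less precise than the data allow and its form is not fixed. Adjustment helps at every correlation in the assumed range, by an amount that depends on r: modestly at 0.5 and substantially from about 0.7 upwards. The gain matters chiefly if the true effect is smaller than planned, because power at 0.29 L is already adequate. The sizes rest on the SDs in section 2.4, on 121 analysed per arm, and on the assumed values of r and of the smaller effect. That the paired tests cannot by themselves show efficacy rests on the design alone, because both arms receive the same background treatment and advice.

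**What to change.** Amend section 3.7 before unblinding:

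- Make the primary comparison at 18 months, the time point used for sizing, an ANCOVA of post-bronchodilator FEV1 with baseline post-bronchodilator FEV1 as covariate, or a repeated-measures model over the visits with the same covariate. Report the adjusted difference with its 95% CI.
- Name this as the single primary method. Use robust or unequal-variance standard errors in place of the variance pre-test and the data-driven choice between t test and rank-sum test.
- Adjust the continuous secondary change outcomes for their own baseline values. A change score alone has SD 0.691 × √(2(1 − r)), which at r = 0.5 is again 0.691 and so gains nothing over the raw value, whereas ANCOVA does.
- Report within-arm changes descriptively, without P values.

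The cost is a change of wording and the ethics approval that section 2.2 requires for any protocol change. The baseline spirometry is already collected, and the sample size can stay as it is.

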## Introduction

1

Chronic obstructive pulmonary disease (COPD) is the third leading cause of death worldwide.^[1]^ and contributes to high morbidity and mortality in China.^[2]^ Exacerbations of COPD negatively affect ^[3]^ the condition of the participants’ health and result in a rapidly increasing risk of death, which brings them huge economic and psychological burden.

According to The Global Initiative for Chronic Obstructive Lung Disease (GOLD),^[4]^ the prevention of exacerbations is the major treatment goal for participants with COPD. A large epidemiological study released by the Chinese Center for Disease Control and Prevention in 2018 showed that up to 92.7% of Chinese adult COPD patients are in GOLD stage 1–2,^[5]^ presenting with now very mild or no significant respiratory symptoms, such as movement restriction and dyspnea.^[6]^ For them, the prevention of exacerbations is of great significance.

Traditional Chinese medicine (TCM) has gradually gained worldwide recognition. TCM, which many participants suffered from COPD turn to for help in China, may provide further options for COPD treatment.^[7]^ Recorded in formulary of peaceful benevolent dispensary, Shenling Baizhu Powder has been used in China for more than 900 years, and its clinical efficacy and safety are recognized. Modified Shenling Baizhu Powder comprises 12 herbs including LABLAB SEMEN ALBUM (Bai bian dou), ATRACTYLODIS MACROCEPHALAE RHIZOMA (Bai zhu), PORIA(Fuling), PLATYCODONIS RADIX (Jie geng), NELUMBINIS SEMEN (Lian zi), CODONOPSIS PILOSULA (Dang shen), AMOMI FRUCTUS (Sha ren), DIOSCOREAE RHIZOMA (Shan yao), COICIS SEMEN (Yiyiren), GLYCYRRHIZAE RADIX ET RHIZOMA (Gan cao), Ephedrae Herba (Ma huang), ARMENIACAE SEMEN AMARUM (Ku xing ren).

According to Modern pharmacological studies, Modified Shenling Baizhu Powder has multiple effects such as anti-inflammatory, relieving asthma, antibechic, eliminating phlegm, antioxidant,^[8]^ and the function of immune regulation^[9]^ and improving lung function.^[10]^

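### Time to first exacerbation is a listed outcome, but section 3.7 names no method for a right-censored time and fills missing values with a mean

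*Protocol article*

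**What the plan says.** Section 3.2 (Outcome measures) lists, as secondary outcomes, "Frequency, interval, duration, and severity of COPD exacerbations; time to first COPD exacerbation". The Introduction gives exacerbations clinical weight. Of patients with GOLD stage 1–2 disease it says: "For them, the prevention of exacerbations is of great significance".

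Section 3.7 (Statistical analysis) sets tests by type of data. Continuous data get a paired t test within group and a t test or rank-sum test between groups. For the rest, "Chi-square test will be used for enumeration data, and rank-sum test will be used for grading data". The section opens by saying that the method should follow the distribution of the data, but no test it then names deals with censoring.

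Three further statements in 3.7 apply to all outcomes. Intention to treat governs every analysis. The full analysis set is described as "including completed cases and dropout cases, excluding censored cases" and the per-protocol set as "including completed cases, excluding dropout cases and censored cases", with the last category undefined. In the full analysis set, "the missing data are substituted by the method of sequence mean value".

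The article makes no power claim for exacerbations. Section 2.4 states: "The sample size was calculated on the primary outcome (the forced expiratory volume in 1 second (FEV1) at 18 months".

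**The concern.** A participant with no exacerbation by dropout or by month 18 has no observed event time. What is known is that the time exceeds the follow-up. A t or rank-sum test on times needs a number for everyone, so such a participant must be left out, given a substituted value, or assigned an arbitrary time. Section 3.7 states only one of these rules, the sequence mean.

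Omission compares times only among people who had the event. That conditions on the outcome and discards most of the information about risk, which lies in how many people stay event-free. Mean substitution gives the participants who did best the average time of those who did worst. Under either rule the trial would probably report no difference in time to first exacerbation even if the hazard were halved.

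A smaller issue concerns frequency. The named tests compare counts without regard to how long each participant was observed.

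**Working it through.** **The plan's own figure.** Section 2.4 gives FEV1 means of 2.54 and 2.83 and SDs of 0.65 and 0.73. With two-sided alpha 0.05 and 90% power (the power is not stated):

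n = (0.65² + 0.73²)(1.960 + 1.282)² / 0.29² = 0.9554 × 10.51 / 0.0841 ≈ 119.4, so 120 per group, or 121 with the t distribution.

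The stated 121 reproduces, and 121/0.9 rounds up to the planned 135. This concerns FEV1 only; what is used below is 135 per arm and 10% dropout.

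**Inputs for the check.** From the article: 135 per arm, 18 months (6 treatment, 12 follow-up), 10% dropout, two-sided 0.05. Assumed, because the article gives none: control 18-month risk 40% (range 30–50%), hazard ratio (HR) 0.65 or 0.5, exponential event and dropout times.

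**Expected events at 40% risk.** Cumulative hazards over 18 months are H = −ln 0.6 = 0.511 for control and D = −ln 0.9 = 0.105 for dropout. The proportion seen to have an event is H/(H+D) × [1 − exp(−(H+D))].

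- Control: 0.381, or 51.5 of 135.
- HR 0.65 (H = 0.332): 0.269, or 36.3 of 135.
- HR 0.5 (H = 0.255): 0.214, or 28.9 of 135.

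**Log-rank.** Power ≈ Φ(|ln HR| × √(events/4) − 1.96).

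- HR 0.65: 0.431 × √(87.8/4) − 1.96 = 0.06, power 52%.
- HR 0.5: 0.693 × √(80.4/4) − 1.96 = 1.15, power 87%.

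Simulation gives 53% and 88% (41–63% and 76–93% over control risks of 30–50%).

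**Times among those with an event only.** At HR 0.65 the simulated mean times are 8.1 and 8.4 months. Event times are close to uniform over 18 months, so their SD is about 18/√12 = 5.2. The standard error is 5.2 × √(1/51.5 + 1/36.3) = 1.13, and the ratio is 0.3/1.13 = 0.27. Power ≈ Φ(0.27 − 1.96) + Φ(−0.27 − 1.96) = 0.046 + 0.013 ≈ 6%. Simulation gives 5–6% at HR 0.65 and 6–7% at HR 0.5, and 5–9% over control risks of 30–50%.

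**Times with the mean filled in.** With one overall mean for both arms, simulated power stays at about 5–7%, essentially the false-positive rate. The article does not say whether the mean is overall or by arm. Filling by arm fails differently: with a fraction p observed, the computed standard error is about p times the true one. At p = 0.381 with no effect, the effective critical value is 1.96 × 0.381 = 0.75, and the false-positive rate is about 45%.

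**Chi-square on any exacerbation.**

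- HR 0.65: 0.381 v 0.269, pooled 0.325, standard error √(2 × 0.325 × 0.675/135) = 0.057, z = 1.97, power ≈ 50%.
- HR 0.5: 0.381 v 0.214, pooled 0.298, standard error 0.0557, z = 3.00, power ≈ 85%.

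Simulation gives 51% and 86%, within about two points of log-rank.

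**Frequency.** Overdispersed counts were simulated with assumed control rates of 0.3 to 1.2 per patient-year, dispersion 0.7 and rate ratio 0.6. Rank-sum on counts has 54–85% power, against 59–92% for a rate-ratio test that uses follow-up time, a loss of 5 to 10 points. The t test on counts loses only 1 to 2. With no effect and 5% v 15% dropout (rate 0.8), the unadjusted tests reject about 6.5% of the time, against about 5.3% for the methods that use follow-up time.

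**The case against.** Section 3.7 gives generic rules by data type and assigns no outcome to a test. It does not say that event-free participants are dropped, and an article may leave survival methods to an analysis plan that is not shown. Named tests can also be used sensibly: chi-square on any exacerbation, or a rank-sum test with event-free participants set to 18 months (51% and 87% power at HR 0.65 and 0.5). These are secondary outcomes without a power claim.

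Much of this stands, and it rules out three stronger readings.

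- A reader might infer that the plan cannot detect an effect on exacerbation risk. It can, by chi-square or by tests on counts.
- A reader might take *censored cases* to mean participants without an exacerbation. In 3.7 the term is a category of participant, set against completers and dropouts, and it also governs the baseline data. Read that way, it would strip event-free people from the baseline table and the FEV1 analysis. Someone who finishes 18 months without an exacerbation is more naturally a completed case.
- A reader might infer a material bias in frequency. That needs unequal dropout between arms, which the article does not suggest, and the effect is small even at 5% v 15%.

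The appeal to an unseen plan does not dispose of the point. The article does more than omit a method: it fixes a list of tests and a substitution rule for missing values, and applying these to event times gives a wrong result. Setting event-free participants to 18 months is not a rule that 3.7 states, and it would credit dropouts with time they were not observed.

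**Conclusion.** The point holds for time to first exacerbation and, to a minor degree, for frequency. No test named in 3.7 handles a right-censored time, and the one stated rule for missing values is invalid for it. If event-free participants are omitted or given an overall mean, power to compare times is about 5–7% at 40% control risk, against about 53% (HR 0.65) and 88% (HR 0.5) for log-rank.

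The power figures rest on assumed event rates, hazard ratios and exponential times. The contrast persists across control risks of 30–50%. The low power depends on omission or mean filling; it does not describe every use of the named tests. The change should be made, but it does not touch the primary FEV1 analysis or the sample size.

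**What to change.** In section 3.7:

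- Analyse time to first exacerbation by Kaplan–Meier curves, a log-rank test and a Cox hazard ratio in all randomised participants, with event-free participants censored at last contact or 18 months.
- Analyse exacerbation frequency by a negative binomial rate ratio with log follow-up time as offset.
- State that sequence-mean substitution does not apply to these outcomes.
- Define *censored cases* so that the term removes no randomised participant from these analyses, in line with the stated intention-to-treat principle.

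The cost is two or three sentences and standard software. No new data are needed.

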In China, Shenling Baizhu Powder is widely used for respiratory diseases. Thus, it is reasonable to hypothesize that Modified Shenling Baizhu Powder is effective for the treatment of COPD. However, few published data show a meaningful effect of Modified Shenling Baizhu Powder on preventing exacerbation and its long-term (18 months) safety profile in participants with COPD of GOLD stage 1 or stage 2. To resolve these issues, we design this randomized, placebo-controlled , double-blind, prospective study protocol.

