The study has some limitations. First, since the study was conducted in Sichuan, China, the relative effects of the test drugs are unclear whether they would be comparable among other ethnic groups. Second, in clinical practice, participants with pure COPD are rare and most of them are associated with other diseases such as hypertension, diabetes, and coronary heart disease. Therefore, the utility (extrapolation) of the results of this study is unclear and requires further evaluation. That said, the results shall aid the decision-making process for COPD therapy and management as well as provide important information which could be incorporated into guidelines for future treatment. A multicenter randomized controlled trial should be conducted in the future, to investigate a large sample of COPD participants and implement a multidimensional comprehensive evaluation.

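### The Introduction sets exacerbation prevention as a question the trial will resolve, but five unranked secondary measures, each judged at an unadjusted P<.05, could answer it

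*Protocol article*

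**What the plan says.** The Introduction (section 1) presents prevention of exacerbations as the main treatment goal in COPD. It then identifies the evidence gap: "few published data show a meaningful effect of Modified Shenling Baizhu Powder on preventing exacerbation and its long-term (18 months) safety profile". The next sentence gives the purpose of the trial: "To resolve these issues, we design this randomized, placebo-controlled , double-blind, prospective study protocol".

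Section 3.2 makes post-bronchodilator FEV1 the primary outcome, and section 2.4 sizes the trial on FEV1 at 18 months. Exacerbations are among the secondaries: "Frequency, interval, duration, and severity of COPD exacerbations; time to first COPD exacerbation". The list has a common time heading, "Secondary outcomes: at 1, 3, 6, 9, 12, 15, 18 months". No secondary is ranked above another.

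Section 3.7 applies one significance rule throughout: "Bilateral tests will be used for all tests, with *P* < .05 indicating a significant difference". The Discussion (section 4) expects the results to "provide important information which could be incorporated into guidelines for future treatment".

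**The concern.** Only secondary outcomes can answer the exacerbation question, and the article does not say which one does. The five measures can disagree: a treatment might shorten episodes without making them rarer, or delay the first without changing the total. Interval and duration are also undefined for a participant who has no exacerbation, so they do not compare everyone who was randomised.

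Since each measure counts as significant below .05, a statement that the formula prevents exacerbations could rest on whichever measure crossed the line. The same holds for the lung-function and questionnaire secondaries. A reader would take 5% as the error rate behind such a statement, and the true rate is higher.

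**Working it through.** **Inputs from the article.**
- Two-sided 0.05 per test, unadjusted (section 3.7).
- Secondary efficacy outcomes (section 3.2): four lung-function measures (pre-bronchodilator FEV1, FVC, FEV1/FVC, FEV1%pred), three scores (mMRC, CAT, SGRQ), five exacerbation measures, and rescue medication use. 4 + 3 + 5 + 1 = 13. Cost-benefit, smoking status and safety are not counted.
- Seven visits in the heading of the secondary list.

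**Assumed.** The article gives no correlations between test statistics. I use 0.5 as the central value, with a range from 0.8 to 0.

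**The plan's own figure.** The article states no family-wise error rate. Its one computed figure is the sample size, which concerns FEV1 only. The difference is 2.83 − 2.54 = 0.29 and the pooled SD is √[(0.65² + 0.73²)/2] = 0.691. With two-sided 0.05 and 90% power (power is not stated; 90% reproduces the figure), n = 2 × (1.960 + 1.282)² × 0.691² / 0.29² ≈ 120 per group, or 121 with the t distribution. This matches the stated 121, and 121/0.9 rounds up to 135 per group. So the sizing is sound for FEV1; it does not cover exacerbations.

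**Step 1: one test per outcome, no true effect.** With independent tests, the chance of at least one rejection among k is 1 − 0.95^k. Counting only results in the formula's favour, it is 1 − 0.975^k.
- k = 5: 1 − 0.95⁵ = 22.6%; favourable only, 1 − 0.975⁵ = 11.9%.
- k = 13: 1 − 0.95¹³ = 48.7%; favourable only, 1 − 0.975¹³ = 28.0%.

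With common correlation ρ, the chance is 1 − ∫ φ(u) [Φ((1.96 − √ρ·u)/√(1−ρ)) − Φ((−1.96 − √ρ·u)/√(1−ρ))]^k du. For favourable results only, the second Φ term is dropped.

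| Family | ρ = 0.8 | ρ = 0.5 | ρ = 0 |
|---|---|---|---|
| 5 exacerbation measures, either direction | 12.7% | 18.3% | 22.6% |
| 5 exacerbation measures, favouring the formula | 6.4% | 9.2% | 11.9% |
| 13 secondaries, either direction | 19.2% | 33.4% | 48.7% |
| 13 secondaries, favouring the formula | 9.6% | 16.7% | 28.0% |

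For the five exacerbation measures, the multiple of the nominal rate is 12.7/5 ≈ 2.5 to 22.6/5 ≈ 4.5 in either direction. For favourable results it is 6.4/2.5 ≈ 2.5 to 11.9/2.5 ≈ 4.8.

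**Step 2: repeated visits.** This step covers only the seven lung-function and questionnaire outcomes. It was simulated with correlation 0.5 between outcomes and 0.8 between visits.
- All seven outcomes at seven visits, 7 × 7 = 49 tests: about 55%, with 49 × 0.05 = 2.45 chance results expected. The range is 30% (correlations 0.8 and 0.9) to 80% (0.3 and 0.5).
- Lung-function contrasts at 18 months only, scores at all visits, 4 + 3 × 7 = 25 tests: about 41%, with 25 × 0.05 = 1.25 expected. The range is 24% to 60% at the same correlations.

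Section 3.2 names the change from baseline to 18 months for the lung-function items, which supports the lower count. It also mentions declines under the seven-visit heading, so the higher count remains possible.

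**Step 3: after the fix.** A single named exacerbation measure tested once carries 5%. Bonferroni over the five would use 0.05/5 = 0.01 each, which gives 1 − 0.99⁵ = 4.9% if they are independent.

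**The case against.** The strongest objection is that ranking and multiplicity control of secondaries are commonly left to an analysis plan, which is not shown. On this view the P<.05 sentence is only a general convention. It is true that a missing hierarchy would be no finding by itself. But the article does not leave the matter open. It states an unadjusted rule for all tests, and it states an aim that only secondary outcomes can answer. That combination stands as a point on the text.

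A second objection is that the framing is mixed, and this is fair. The issues named in the Introduction include 18-month safety. The Discussion describes the trial as being about slowing lung-function decline, leaves exacerbations out of its list of focus areas, calls the wider applicability of the results unclear and asks for a larger multicentre trial. This weakens any suggestion that a confirmatory exacerbation claim is promised. It also shows that the article does not settle what role exacerbations have.

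Three stronger readings are tempting, and the documents do not support them:
- **A false exacerbation claim is likely.** The figure is 18%, or 9% in the formula's favour. Only the visit-by-visit counts pass one half, and those contain no exacerbation outcome.
- **The 49-test figure is the plan's error rate.** It is an upper reading of section 3.2.
- **The plan lets a secondary result stand in for a failed primary.** No sentence says so. The article simply does not limit what a significant secondary result may be used for.

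**Conclusion.** The point holds as a mismatch between the stated aim and the way its outcomes are fixed. Exacerbation prevention is put forward as a question to be resolved, no single measure is named to answer it, and five measures are each judged at .05. The resulting error is about 2.5 to 4.8 times nominal for the exacerbation family, whether or not direction is counted. This conclusion needs no assumption about visits. It rests on one test per measure and on assumed correlations between 0 and 0.8. Visits add to the error for the other secondaries by an amount that the article leaves uncertain. The primary FEV1 comparison and the sample size are not affected. It should be corrected, but it does not undermine the design.

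**What to change.** In section 3.2, name one exacerbation measure that is defined for every randomised participant as the single key secondary, for example the rate per person-year over 18 months. In section 3.7, limit the P<.05 rule to the primary and that key secondary. Testing the key secondary in fixed sequence after the primary is one way to do this, not the only one. Label all other secondary outcomes and visits exploratory, and report them as estimates with 95% confidence intervals.

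Alternatively, label all exacerbation results exploratory and reword the Introduction to say that FEV1 decides the trial.

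Either route changes wording only and needs no extra participants, visits or data. The cost is that the other secondary results can no longer be called significant. Under the fixed sequence, the exacerbation claim also depends on the primary succeeding.
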